### 2.2 Research design

The research study is designed to deliver the research objectives, which are to:

Generate empirical data and build theory on the relationship between legal consciousness, legal norms, and legal practices and experiences of sexual violence and sexual autonomy in different models of governance;Generate empirical data and build theory on how marginalised groups (sex workers) interpret the sexual violence they experience, their rights regarding sexual violence, how and whether they seek redress through the criminal justice system, and outcomes in different models of governance;Generate empirical data and build theory on how various criminal justice institutions respond to sexual violence among various sex-working populations in both theory (law and legal norms re consent) and practice (police actions, reporting systems, court dispensation) in different models of governance;Account for differences among groups of sex workers by gender, age, ethnicity, sexual orientation, citizenship, and sex market, especially for trans, MSM sex workers, and migrant communities;Build knowledge of how researchers and expert advisors can work together in the research process to interpret findings and build theory, and empower expert advisors with evidence for better practices;Generate and disseminate evidence-based information on best practices to help provide justice for sex workers.

#### 2.2.1 Research questions

The research questions (RQs) for the project are as follows:

RQ1 What is the frequency of sexual violence as reported by the diversity of sex workers, and what are the characteristics and nature of their reporting of sexual violence?

RQ2 How do different parts of the criminal justice system (police, lawyers, judges) respond, record, investigate and prosecute reports of sexual violence against sex workers?

RQ3 How do sex workers experience the reporting, recording, investigation and prosecution of sexual violence? How do sex workers experience court processes when crimes enter the criminal justice system?

RQ4 What processes and policies (sentencing guidelines or other legal norms) include sex work explicitly and, if they do, how does this influence how police, prosecutors and other agencies respond?

RQ5 How does the response, recording, investigation and prosecution or reports of sexual violence vary by community of sex worker (gender, race, ethnicity, sexuality, citizenship, sex market)?

RQ6 How do legal regimes differ in how parts of the criminal justice system (police, judges, attorneys, witnesses) respond to sexual violence against sex workers?

RQ7 How has consent, conditional consent and non-consent by sex workers been recognised historically? What are the current legal norms with regards to rape and sexual assault and conditions of consent?

RQ8 What and how are the conditions of consent understood and negotiated by sex workers? How do they understand violations of consent and their legal rights?

RQ9 How is consent and conditional consent (e. g., cases where condoms were removed and non-payment) classified in different legal systems, (e. g., as fraud or sexual violence)? How does this compare to sex workers’ own perceptions of harm?

RQ10 How do understandings and negotiations of consent vary by community of sex worker (gender, race, ethnicity, sexuality, citizenship, sex market)?

RQ11 How do understandings and negotiations of consent vary by legal system?

RQ12 From the empirical findings, are there examples of good practice in supporting sex workers at various levels and stages of criminal justice interactions, including sex worker or witness support services?

RQ13 Are there other forms of justice that survivors report, and what do these look like?

#### 2.2.2 Study setting

We will address the research questions above by comparing four different legal environments: legalisation (Nevada USA) where legal brothels are permitted in 10 of Nevada’s 17 counties; client criminalisation (Northern Ireland) whereby following the Nordic model, paying for sexual services is now a summary offence with a maximum penalty of 12 months in prison; decriminalisation (New Zealand) where prostitution, including the operation of brothels is permitted subject to municipal regulation and partial criminalisation (England, Scotland and Wales) whereby the act of selling sex itself is not illegal, but laws have been drafted around a number of facets of sex work such as brothel keeping, soliciting, living of the proceeds of prostitution and so forth.

#### 2.2.3 Study period

The study began in July 2021 and data collection is taking place across an estimated 11-month period from March 2022 to February 2023. The end date of survey data collection will depend on the point at which a sufficient sample is achieved for the survey in each jurisdiction.

### 2.3 Data collection

This is a mixed methods (quantitative and qualitative) research study, comprising three work packages:

Work Package 1: An online survey of sex workers (n = 1,000) will gather data on experiences of sexual violence in sex work across the research sites. It will analyse harms, reporting, consent, non-payment, condom removal, experience of police and support services and be analysed according to socio-demographic of respondent and sex work sectors. This will be used to answer Research Questions 1, 3, 5, 8, 10 and 13. Recruitment will be through key online sex work platforms and NGO/health outreach and support services for sex workers.

Work Package 2: Interviews with victim-survivors of sexual violence in sex work (n = 10 per research site), practitioners from NGOs and health providers, police, lawyers and prosecutors (n = 10 per research site) will explore reporting, signposting, investigation, trauma management and criminal justice system experiences. The interview sample sizes aim to reach thematic saturation at 10 practitioners (including criminal justice professionals) and 10 sex workers each of the four sites. As a minimum, 6 interviews from each group in each site should provide an 80% saturation of themes at ≤5% new information [24]. These interviews will be used to answer Research Questions 2, 4, 6 and 12. Recruitment will be through Advisory Group members and partner organisations. Peer researchers with a lived experience of sex work / sexual violence will be trained to conduct interviews with sex workers.

Work Package 3: A desk analysis of legal norms and relevant case law will assist us to understand how the legal system operates in different jurisdictions and explore how consent, violence and sex work are operationalised in legal judgements. This analysis will be used to answer Research Questions 7, 9 and 11.

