**Methods:**

An international survey (n = 1,000) will be translated into several languages, to disaggregate experiences by demographic categories (gender, ethnicity, sexual orientation) and sex work sector (including online, street-based and brothels). Interviews (n = 100) with sex workers, police, prosecutors and service providers will be thematically analysed to explore legal consciousness, why the patterns occur and contextualise the statistical findings. These data will be supplemented with comparative legislative, policy and case analysis. Research study data will be used to compare the social factors and legal norms shaping sex workers experiences of sexual violence, justice and support interventions. Recommendations for a ‘best practice’ review of legal improvements and support interventions will be produced following completion of the study.

Given the sensitive nature of the research, robust ethical and data protection mechanisms are in place. The research has ethical approval from each research site, an Advisory Board and trained, paid peer researchers to assist with data gathering, analysis and dissemination. The study will report findings in 2023/2024.

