#### 2.3.5. Survey sample size

Despite the frequent experiences of violence in some forms of sex work, accessing workers with violent experiences among the entire population of sex workers can be challenging. This population is often under-represented in standard sexual violence surveys, which prevents weighting methodology being employed in this study–this is because there are not sufficient existing independent data with which to compare populations. In other sex work contexts, too many invitations to participate in studies targeted at a few individuals, stigma, and working without legal protection can mean some sex workers are reluctant to engage with research [37].

Unfortunately, the sample for this survey cannot be randomised, as too few responses would be received and there are no intervention arms in this study or reliable population estimates in the sites [38]. However, stratified sample groups for distribution by sector and site have been designed for the recruitment, to attempt to ensure as far as possible that no under- or over-representation of one particular sector of sex work in each research site.

To ensure that we achieve an adequate sample size, calculations were made to test our null hypothesis, namely that there is no difference in the experience of sexual violence by jurisdiction. We used the chi-squared test to test for independence of outcome (binary Yes, No) and jurisdiction (4 levels) with 3 degrees of freedom. Since a significance level of 5% is desired, the chi-squared statistic would need to exceed 7.81. To test the null hypothesis, a minimum sample size of 1760 respondents for the survey would be required, with a minimum of 440 respondents in each jurisdiction.

We derived an alternative hypothesis from a low conservative estimate from Deering et al [39], that circa 15% of sex workers experience violence. We anticipated the overall probability of sexual violence at 15% across all 4 jurisdictions, with 2 jurisdictions differing by 10 points (ie. one records 10% and the other 20%) to be detectable at least 80% of the time. We calculated that we would need a maximum sample size of 3200, where p = 55%. Fifty-five per cent was our upper estimate of sexual violence in sex work [40]. The chi-squared statistic was 7.84 from this calculation.

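### The survey size is given as 1,000, 1,760 and 3,200 without reconciliation; on the plan's own test and rates 1,000 gives about 75% power, not the stated 80%, and 1,760 gives about 95%

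*Protocol article*

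**What the plan says.** **Survey size.** The Abstract (Methods) states "An international survey (n = 1,000) will be translated into several languages", and section 2.3, Work Package 1, repeats it: "An online survey of sex workers (n = 1,000) will gather data on experiences of sexual violence". Section 2.3.5 says that testing the null hypothesis of no difference by jurisdiction needs "a minimum sample size of 1760 respondents for the survey would be required, with a minimum of 440 respondents in each jurisdiction". Its next paragraph adds an upper figure: "We calculated that we would need a maximum sample size of 3200, where p = 55" per cent.

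**Test and effect.** Section 2.3.5 uses a chi-squared test of independence of "outcome (binary Yes, No) and jurisdiction (4 levels) with 3 degrees of freedom", at 5%, with critical value 7.81. The alternative is an overall 15%, "with 2 jurisdictions differing by 10 points (ie. one records 10% and the other 20%) to be detectable at least 80% of the time".

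**When the survey closes.** Section 2.2.3 ties the end date to reaching a sufficient sample in each jurisdiction. Section 2.3.2 sets February 2023, or a sufficient sample, within the study's time constraints. Section 2.3.6 has a mid-point analysis that can trigger more recruitment where numbers are short. None of the three gives a number.

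**Allocation.** Section 4.3 notes that the population is small, particularly in Northern Ireland.

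**Interviews.** The Abstract has "Interviews (n = 100) with sex workers, police, prosecutors and service providers will be thematically analysed". Work Package 2 has "10 practitioners (including criminal justice professionals) and 10 sex workers each of the four sites".

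**The concern.** The planned size is 1,000/1,760 = 57% of the minimum that the same article sets. Split equally, it is 250 per jurisdiction against 440. The comparison of jurisdictions is the study's stated hypothesis, so the size on which it rests should be one number with a known power.

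The closing rule and the mid-point recruitment check also depend on this number. A team that stops at 1,000 and a team that stops at 1,760 could each claim to follow the article. If the survey ends near 1,000 and the test is not significant, a reader who relies on the stated 80% will give that result more weight than it can bear, in a study meant to support legal recommendations.

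**Working it through.** **Inputs.** Test, df, 5% level, overall 15%, and one jurisdiction at 10% and one at 20%: section 2.3.5. The other two rates are not stated; 15% each is implied by the overall 15% under equal recruitment. Equal recruitment is taken from the 440-per-jurisdiction figure.

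**Formula.** For rates p_i and equal groups, w² = mean[(p_i − p̄)²] / [p̄(1 − p̄)]. The noncentrality is λ = N·w², and power = P(χ²₃(λ) > 7.815). Power of 80% needs λ = 10.90.

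**The plan's figures first.** The critical value reproduces (7.815). For 10/15/15/20%:

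- Sum of squared deviations = 0.05² + 0 + 0 + 0.05² = 0.005.
- w² = (0.005/4)/(0.15 × 0.85) = 0.00125/0.1275 = 0.00980.
- N for 80% power = 10.90/0.00980, about 1,112 (278 per jurisdiction).
- At N = 1,760, λ = 17.25 and power is 95.1%.

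So 1,760 does not reproduce as an 80% figure. On these inputs, 90% power needs 1,445 and 95% needs 1,751, so 1,760 sits at about 95%. Other four-rate patterns around 15%, and pairwise 10% v 20% calculations with and without correction for multiplicity or continuity, did not give 1,760 at 80% power either.

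**Power at 1,000.** λ = 1,000 × 0.00980 = 9.80, power 75.2%. A simulation of 200,000 tables gives 75.8%. The 10% v 20% gap would have to widen to about 10.5 points for 80%.

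**At 55%.** The plan gives 3,200 here but no gap. Assuming the same 10 points, as 50/55/55/60%, w² = 0.00125/(0.55 × 0.45) = 0.00505.

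| N (equal split) | 10/15/15/20% | 50/55/55/60% (assumed) |
|---|---|---|
| 1,000 | 75.2% | 44.5% |
| 1,760 | 95.1% | 70.5% |
| 3,200 | 99.9% | 93.7% |
| N for 80% power | about 1,112 | about 2,160 |

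Under this assumption 3,200 is not an 80% figure either. Since the article states no gap for it, it cannot be checked further.

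**Unequal recruitment.** Suppose Northern Ireland supplies n of the 1,000 and the rest is split equally (assumed). Now λ = Σ n_i(p_i − p̄)² / [p̄(1 − p̄)], with p̄ the weighted mean of the same four rates.

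| Northern Ireland n | its rate 10% | its rate 20% | its rate 15% |
|---|---|---|---|
| 50 | 47% | 54% | 85% |
| 100 | 57% | 62% | 83% |
| 150 | 65% | 68% | 81% |

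**Interviews.** 4 sites × (10 + 10) = 80, against 100 in the Abstract.

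**The case against.** **1,000 is not a cap.** This is fair: sections 2.2.3, 2.3.2 and 2.3.6 leave room to recruit beyond it, so the power at 1,000 is conditional on closing there. What does not stand is that these sections resolve the conflict. They rest on a sufficient size that is never given a number, and the time limit may bind first.

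**Missing 1,760 means losing 80% power.** A reader might infer this, since the two statements stand close together. The article does not support it. The sentence with 1,760 carries no power; the 80% appears in the following paragraph with the 15% alternative and the 3,200. The arithmetic is against it too: any balanced total from about 1,112 to 1,759 misses the stated minimum and still has at least 80% power on the 15% scenario. The shortfall at 1,000 has to be shown by direct calculation.

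**The shortfall is small and depends on the pattern.** On the plan's own scenario it is about 5 points. A single unadjusted comparison of 10% with 20%, at 250 each, has 88% power, and a 10/10/20/20% pattern has 97% on the 3-df test. But the article specifies the four-level test with two jurisdictions differing around an overall 15%, so 75% is the relevant figure.

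**The 45% figure is not the plan's.** Correct: it rests on an assumed gap at 55% and cannot be set against a promised 80% at that rate. It shows only what 1,000 would deliver if the same gap were of interest there.

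**Unequal recruitment need not hurt.** Also correct. If the small jurisdiction holds a middle rate, power exceeds 80%.

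**Conclusion.** The point holds. Three survey sizes stand unreconciled, and the stated power matches neither the planned size nor the stated minimum: 1,000 gives about 75%, 1,760 about 95%, and 80% needs about 1,112.

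On the plan's own scenario the power shortfall is modest. It becomes large only under assumptions that the article does not make: a 10-point gap around 55% (about 45% power at 1,000), or few respondents from a jurisdiction with an extreme rate (down to about 47%). The 75% rests on the 3-df test, the two unstated rates being 15%, and equal recruitment. It applies only if the survey closes at 1,000.

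The inconsistency itself is certain from the text. The interview mismatch is a separate, minor point and has no bearing on power.

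**What to change.** - Give one survey target in the Abstract, Work Package 1 and section 2.3.5, and name it as the sufficient size in sections 2.2.3, 2.3.2 and 2.3.6.
- If 1,000 stands, remove the 1,760/440 requirement and the 80% statement. State about 75% power for 10% v 20% around 15% at equal allocation, and add the gap assumed at 55% with the power that results (about 45% if that gap is also 10 points).
- If 1,760 is kept, state its power as about 95% on the 15% scenario, not 80%.
- State the gap and power behind 3,200, or drop the figure.
- Give expected counts per jurisdiction, with a realistic one for Northern Ireland, and the power at those counts.
- Separately, correct the interview total to 80 or say where the other 20 come from.

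If 1,000 is the size the team expects to reach, the cost is wording only, and the stated power becomes less favourable. A higher target would need more recruitment within the same time limits.

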## 2. Materials and methods

### 2.1 Research aims

The overarching question this study seeks to address is how social, legal, and judicial contexts shape the safety and well-being of people engaging in sex work and, in particular, how context shapes experiences of sexual violence.

Our aims are threefold:

1. Theoretical: to explore sex workers’ experiences and prevalence of sexual violence against the legal norms and boundaries in each of the four legislative models, also examining the least investigated inflictions such as ‘stealthing’ (removal of condom without permission). A desk analysis of legislation and case law in each site, regarding sexual violence and how these laws were operationalised for sex workers. This will assist us to understand how the legal system operates in different jurisdictions and explore how consent, violence and sex work are incorporated in legal judgements. These will be analysed for characteristics, perpetrator, outcome, and tariff.

2. Empirical: to enhance what is known about sex workers’ experiences of the criminal justice system by gathering and analysing new empirical data on how the system operates in different jurisdictions, looking at the impact of legislative models on how sexual violence is responded to, the impact of different settings, and attrition, outcome, and conviction. This will be applied across the four study locations through online surveys of sex workers on sexual violence, which will measure prevalence, experiences, attitudes and understandings of the law, experiences with the police, courts and other agencies, support received and interventions.

3. Practice-based: to facilitate the integration of best practice from a review of what works regarding supporting victims into safety and health-related provision, policies and agencies, led by ‘experts by experience’. These experts are four peer researchers who are sex workers / survivors of sexual violence, who will be trained in research skills, and work as a core part of the research team to interview sex workers who have experienced sexual violence (n = 10 per research site). The research team will also conduct interviews with practitioners (NGOs and statutory health service professionals), police, and criminal justice personnel (n = 10 per research site) to assess issues such as reporting, signposting, available resources, therapy, and criminal justice support.

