The survey will be launched in September 2022, with data gathered simultaneously in all sites. The survey will remain open until February 2023 (or until a sufficient sample size has been reached for statistical significance, within the time constraints of the study). The survey will be translated into Portuguese, South American (Brazilian) Spanish, Romanian, Filipino, Thai and Mandarin; these languages have been identified as the most crucial to reach migrant sex workers in the research sites.

Respondents will be recruited through the project Advisory Boards in each research site, adult sex work platforms and NGOs delivering outreach with sex workers, as well as via the broader project teams’ connections with sex work communities. Given the hard-to-reach nature of sex working populations and the sensitivity of sexual violence, random sampling methods are not appropriate for this study. Therefore, non-random strata sampling by sector and demographic group will be employed.

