### 3.3. Advisory boards

Four Advisory Boards have been recruited to cover the individual sites: Northern Ireland; ESW, Nevada; and New Zealand. There is an Academic Advisory Board for the project which covers all sites. The Boards exist to provide a forum for discussion, feedback, oversight, guidance, meaningful involvement and independent advice to support the integrity and value of the research, following best practice [55].

Three of these Boards provide guidance in each geographical research site. Members were invited by the Research Team at the start of the study. The Boards comprise;

‘Experts by experience’ who are sex workers with lived experience;NGOs that are sex worker-led organisations and/or that work or have worked in supporting survivors of sexual violence;Academics working in the field.

The fourth Advisory Board is an Academic Advisory Committee for the study, covering all the research sites. This Board comprises internationally renowned experts who are providing specific and technical guidance and oversight for the whole study, particularly around methodology, analysis and reporting of results.

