### 4.3. Study limitations

There is no existing international survey of legal consciousness and/or violence against sex workers on which to build comparative results, so future replicability cannot be entirely assured. However, the transparent reporting of methods in this protocol and robust statistical tests employed should assist in future replication of this study.

Regrettably, the survey sample cannot be randomised, given the population size, sensitivity of the research and the small size of the sex working population (particularly in Northern Ireland). Online sex workers cannot be recruited simply in jurisdictions where it is illegal. Blinding of participants into different cohorts is not possible, given the lack of consistent or standard interventions on which to assess the validity of outcomes. Data are self-reported and gained through existing networks, which may result in self-selection bias from respondents and the under-representation of certain groups in results.

Inference from these data gathered in the study sites (all English-speaking, high-income countries) cannot be made to the Global South or populations of sex workers operating in other contexts.

Given the short length of the project data gathering phase, longitudinal follow-up is not possible with this cohort. The sample cannot include sex workers in prison or hospital due to ethical restrictions. It is not possible to interview people about current, ongoing legal cases so as not to risk transcripts being requested as evidence and biasing proceedings.

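### The survey is presented as measuring prevalence and comparing jurisdictions, but recruitment route may be related to victimisation, its mix can differ by site, and the stated strata and limitations do not address it

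*Protocol article*

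**What the plan says.** - **Target.** Aim 2 (section 2.1) describes "online surveys of sex workers on sexual violence, which will measure prevalence". RQ1 (section 2.2.1) asks for the frequency of reported sexual violence. Sections 2.3.5 and 2.3.6 set the null hypothesis that victimisation does not differ by jurisdiction.
- **Routes into the sample.** Work Package 1 (section 2.3): "Recruitment will be through key online sex work platforms and NGO/health outreach and support services for sex workers". Section 2.3.2: "Respondents will be recruited through the project Advisory Boards in each research site, adult sex work platforms and NGOs delivering outreach with sex workers", to which it adds the team's own contacts in sex work communities.
- **Who sits on the Boards.** Section 3.3 lists sex workers with lived experience, academics, and "NGOs that are sex worker-led organisations and/or that work or have worked in supporting survivors of sexual violence".
- **Availability of routes.** Section 4.3: "Online sex workers cannot be recruited simply in jurisdictions where it is illegal".
- **Control of the sample.** Section 2.3.2: "non-random strata sampling by sector and demographic group will be employed". Section 2.3.5 adds distribution groups by sector and site, intended to keep any one sector from being over- or under-represented, and explains why weighting is not possible.
- **Analysis and caveat.** Section 2.3.6 names jurisdiction and socio-demographic categories. Section 4.3 acknowledges that self-report through existing networks may bring self-selection and leave some groups under-represented.

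**The concern.** The routes are unlike. A person may see the survey on a work platform whether or not they have been assaulted. A person in contact with a support organisation, in particular one that works with survivors, may be there because of an assault. If reported victimisation differs by route, the overall frequency depends on the mix of routes as well as on risk.

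The comparison between jurisdictions is more exposed than the overall figure. Legal regime is the exposure under study, and it may also affect how people can be reached. If one site relies more on services because platform recruitment is hard there, that site's figure can shift for reasons unrelated to risk. Stratifying by sector and demographic group does not settle this. Two online workers of the same gender and age, one reached through a platform and one through a service, fall in the same stratum yet may differ in their chance of having been victimised.

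At stake is how a significant jurisdiction effect would be read. It could be taken as evidence about a legal model when part of it reflects how respondents were found.

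**Working it through.** **Inputs from the protocol article.** Section 2.3.5 gives a low estimate of 15%, an upper estimate of 55%, a 10-point spread to be detected (10% versus 20%), a 5% chi-squared test with 3 degrees of freedom, a critical value of 7.81 and a minimum sample of 1760. Section 2.3 gives a planned n of 1,000.

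**Inputs the article does not give (assumed).** These are the share of respondents arriving through services in each site, and the victimisation rate by route.

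**Step 1: the plan's own figure.** The upper 5% point of chi-squared with 3 degrees of freedom is 7.815, which agrees with 7.81. The plan has no figure for route, so what follows is illustration.

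**Step 2: effect of the mix on a site's figure.** Let p be the rate among platform recruits, q the rate among service recruits (both the same in every site) and s the service share.

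Observed rate = p + (q − p) × s

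Spurious gap between sites A and B = (q − p) × (s_B − s_A)

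With p = 15% and shares of 20% and 50%:

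| q | Site with 20% share | Site with 50% share | Gap | Odds ratio, service vs platform |
|---|---|---|---|---|
| 30% | 15 + 15 × 0.20 = 18% | 15 + 15 × 0.50 = 22.5% | 4.5 points | (0.30/0.70)/(0.15/0.85) ≈ 2.4 |
| 55% | 15 + 40 × 0.20 = 23% | 15 + 40 × 0.50 = 35% | 12 points | (0.55/0.45)/(0.15/0.85) ≈ 6.9 |

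The gap is zero if q = p or if the shares are equal. It changes sign if service recruits report less violence than platform recruits.

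**Step 3: effect on the 5% test with no true jurisdiction effect.** Take four equal sites, p = 15% and service shares of 20/20/20/60%. The noncentrality is λ = N × mean((p_i − p̄)²) / (p̄(1 − p̄)).

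Example at odds ratio 2: the service odds are 2 × 0.15/0.85 = 0.353, so q = 26.1%. The sites show 17.2, 17.2, 17.2 and 21.7%, with mean 18.3%. The shares have variance (3 × 0.1² + 0.3²)/4 = 0.03, so λ = N × 0.03 × 0.111² / (0.183 × 0.817). This is about 2.5 at N = 1000 and 4.3 at N = 1760.

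| Odds ratio | Spurious gap | Rejection, N = 1000 | Rejection, N = 1760 |
|---|---|---|---|
| 1.5 | 2.4 points | 10% | 14% |
| 2 | 4.4 points | 23% | 39% |
| 3 | 7.8 points | 59% | 85% |

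More uneven shares (10/30/50/70%) give gaps of 3.6, 6.7 and 11.8 points, and rejection of 13%, 35% and 80% at N = 1000. A larger sample does not help: it raises the false-positive rate.

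**Step 4: equal mix in all sites.** With a 30% service share everywhere, the test stays at 5%. The overall figure becomes 16.8%, 18.3% or 20.9% instead of 15% for the three odds ratios.

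**The case against.** The case on the other side has real force.

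- **Outcome-dependent entry is not documented.** Section 2.3 speaks of services for sex workers in general, and section 2.3.2 of outreach NGOs. Survivor support appears only in the description of Board members, beside sex worker-led groups, sex workers and academics. A reader might infer that the survey is enriched on its own outcome. The article gives no rate by route and does not support that as fact. This stands.
- **A difference in mix between sites is possible, not stated.** The remark in section 4.3 concerns difficulty in reaching one sector. Other contacts could fill a shortfall. This stands: the mix can differ, not will differ.
- **Direction is open.** A reader might infer that the frequency is inflated. Section 2.3.5 also says stigma and lack of legal protection deter some workers from research, and section 4.3 excludes people in prison or hospital and expects some groups to be under-represented. The net bias could go either way. This stands.
- **Adjusting for route is not a clean cure.** If victimisation or law affects route, a route term or a restriction to platform recruits can itself bias the contrast or remove part of a legal effect. This stands, and it limits the fix to sensitivity analyses.
- **Bias is disclosed, and details may sit elsewhere.** This stands only in part. A model term may belong in an analysis plan, and the questionnaire, which is not shown, may already ask about route. But the caveat in section 4.3 is general. It does not say that selection may be linked to victimisation or may differ between the compared sites. The survey is anonymous (sections 3.1.1 and 3.1.3), so a route that is not recorded at entry cannot be recovered later.

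Random sampling and weighting are reasonably ruled out, and nothing here asks for them.

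**Conclusion.** The point holds in limited form. The article claims to measure prevalence and to test a jurisdiction difference with a non-random sample drawn through unlike routes. Its stated strata and limitations do not address route, so part of a between-jurisdiction difference could reflect how respondents were reached.

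Size and direction cannot be derived from the article. The moderate illustration (30% against 15%) gives 4.5 points, a little under half of the 10-point spread the plan wants to detect. The 12-point figure is a worst case: it assigns the plan's low and upper overall estimates to the two routes, which implies an odds ratio of about 6.9. All of these figures rest on assumed shares and assumed rates by route. They do not show that a finding would be produced by recruitment, only that it could not be told apart from recruitment without information on route.

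This is a cheap improvement that should be made, because it changes what the study can conclude.

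**What to change.** 1. **Record route**, unless the questionnaire already does. Use a separate anonymous link (a copy of the form) per channel and site, or one closed item on how the respondent heard of the survey. A link identifies a channel, not a person.
2. **Report** the frequency of victimisation by route within each site.
3. **Sensitivity analyses.** Show the jurisdiction contrast among platform-recruited respondents only, and with a route term. Place both beside the unadjusted main contrast, not instead of it. State that route may itself be affected by victimisation or by the legal regime, so these analyses do not remove the bias.
4. **Wording.** In section 2.1, claim frequency among respondents instead of prevalence. In section 4.3, extend the self-selection caveat to the comparison between sites.

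**Cost.** One extra item or a set of extra links, small cells and wider intervals in small sites, and a weak platform-only contrast where online recruitment is difficult. Section 3.4 says recruitment was under way in September 2022, so route may be missing for anyone who answered before the change. The wording changes remain possible at any stage.
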